The aforementioned automated clinical trials platform developed by Phelix AI© is a novel platform that automates the “patient research journey”. The research team will input the patient contact information into the Phelix AI© platform and the platform will then automatically start patients along their journey. The specific tasks that this platform will perform for the purposes of this trial include: 1) sending the ICF document; 2) scheduling a telephone follow-up with researchers to discuss the ICF document and complete the informed consent process; 3) send reminders to patients at the 1-week and 2-week points of the intervention period to remind patients to adhere to the study protocol; 4) schedule a post-intervention follow-up appointment with the research team; 5) send a follow-up email to patients two weeks after their scheduled surgery to ascertain whether any adverse events have occurred and whether they have required any care outside of the hospital in which they underwent their index operation; 6) schedule the 30-day postoperative visit with the research team. Neither this platform nor the company will retain or store any patient or research information asides from the patient email address for contact throughout the trial. Phelix’s network and services are cloud native (i.e., built on and benefit from the security measures provided by Google’s Cloud Platform (GCP)). Phelix classifies email address as Personal Data. All data, including Personal Data, is at all times hosted on Canadian servers and resources on Google Cloud Platform. Phelix does not access, share or process Personal Data beyond what is minimally required to enable customers access their Phelix services.  Email addresses used by your organization in its engagement with Phelix are not shared externally, and only shared internally on a need-to-know basis among the Phelix personnel (i.e., the researchers) with whom you will interact by email. Otherwise, at all times, whether in transit or at rest, email addresses are treated as any other Personal Data stored on Phelix, and will be anonymized, encrypted, and securely hosted.

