## What is the proposed frequency and duration of follow up?

Patients will attend follow up with their respective surgeons as per the surgeon’s clinical follow-up schedule for the given procedure. From a research perspective, the patient follow-up protocol will be implemented following initiation of the VLED. See Figure 1 for the SPIRIT diagram depicting the research follow-up protocol. Patients will be followed for a period of approximately 8 weeks. Patients will have in-person baseline measures, including weight, height, waist circumference, hand grip strength, and symptom screening at the time of preoperative VLED initiation, the day of their surgery, and at 30-days following the date of their surgery. On the day of their surgery, patient data will also be collected with regards to compliance with the preoperative VLED. At the one-month follow-up, patients will also complete standardized follow-up questionnaires that will focus on adverse events, symptoms, and postoperative recovery, as well as the 36-Item Short Form Survey (SF-36). Electronic medical records will be reviewed at thirty-days postoperatively to assess for postoperative morbidity and mortality. Both the clinical and research follow-up will be consistent regardless of the arm the patient is allocated to.

| **Activity** | **Before Randomization** | **-23** | **After Randomization** | | | |
| --- | --- | --- | --- | --- | --- | --- |
|  | **-60 to -23** |  | **-23 to -2** | **-2 to 0** | **0 to discharge** | **+30** |
| Eligibility assessment | X |  |  |  |  |  |
| Informed consent | X |  |  |  |  |  |
| Randomization |  | X |  |  |  |  |
| Intervention (i.e., VLED) |  |  | X |  |  |  |
| Baseline demographic data | X |  |  |  |  |  |
| Operative data collection |  |  |  | X |  |  |
| Baseline anthropometrics (including hand grip strength) | X |  |  |  |  |  |
| Post-intervention anthropometrics |  |  |  | X |  |  |
| Post-surgical anthropometrics |  |  |  |  |  | X |
| Intervention-associated adverse events |  |  | X | X | X | X |
| Postoperative morbidity |  |  |  |  | X | X |
| Surgeon perceived difficulty |  |  |  | X |  |  |
| QoL assessment (i.e., SF-36) | X |  |  | X |  | X |
| Intervention adherence |  |  | X | X |  |  |
| Follow-up completion |  |  |  |  |  | X |

*Figure 1.* SPIRIT figure for participant timeline

*VLED, very low energy diet; QoL, quality of life*

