## How will the outcome measures be measured at follow up?

The feasibility measures will be ascertained by the number of patients recruited and the number of patients completing follow-up as recorded on a standardized form by a research assistant, as well as patient reported compliance via a patient-completed diet diary that they will complete daily during the three-week period prior to surgery. Both the treatment and control arms will complete these forms and give them to the research assistant in an opaque envelope on the date of their surgery. Patients in the control arms will be instructed to leave the form blank.

Safety data will be ascertained via a combination of patient self-reporting and electronic medical record data. Paper and/or electronic questionnaires will be used to assess the presence of adverse events at baseline, the morning prior to surgery, and at 30-days postoperatively.

Similarly, efficacy data will be ascertained via review of the electronic medical record. Electronic medical records will be reviewed on the date of surgery and at 30-days postoperatively to assess for any further adverse events and to evaluate 30-day postoperative morbidity. We will assess operative time, intraoperative blood loss, and postoperative length of stay via electronic medical records. The quality-of-life data will be ascertained at baseline, following completion of the VLED, and at 30-days postoperatively via administration of an in-person paper or electronic SF-36 questionnaire. Lastly, anthropometric data (i.e., height, weight, waist circumference, grip strength) will be measured at baseline, the morning of surgery, and at 30-days postoperatively by a research assistant blinded to treatment allocation. This will be recorded and stored via a Redcap© form created *a priori*.

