**Describe the trial steering committee and if relevant the data safety and monitoring committee.**

[name] will be the principal investigator for the present RCT, and part of his responsibilities will be to oversee day-to-day trial management. He will be supported by a steering committee, as well as research assistants and biostatisticians. The steering committee will be involved through study inception until study completion. The steering committee will oversee design, data collection, data management, interpretation of the data, and manuscript generation. This committee will hold the primary responsibility for publication of the trial results. It will be comprised of both clinical and methodologic experts; specifically, the principal investigators, national leaders, and individuals with knowledge in specific areas or in clinical trial methods. [name] will meet with the steering committee at least once during the planning, recruitment, and close-out phases of the trial, and at any other time point as deemed necessary by the principal investigators.

To provide more frequent oversight of the study, a subset of the steering committee will constitute the operations committee. This committee will be composed of a select group of investigators chosen for their specific expertise and experience. The operations committee is ultimately responsible for all decisions regarding the design and conduct of the trial. Outcome adjudication committees and statistical analysis sub-committees blinded to treatment allocation will be formed and oversee data collection, extraction, and analysis. An equity, diversity, and inclusion (EDI) sub-committee will be formed to ensure that all relevant EDI aspects of this trial are identified and managed.

An independent Data Monitoring Committee (DMC) will be established and lead by an independent physician to monitor and adjudicate adverse events throughout the trial. Occurrence of all serious adverse events will be collected, where applicable, in keeping with laws and regulations governing the study site. All serious adverse events will be fully documented on appropriate case report forms outlining onset, duration, treatment required, outcome, and action taken. These data will be iteratively evaluated by the DMC and should there be cause for concern for patient safety moving forward at any point in the trial, they will consult with the principal investigators to discuss premature termination of the study.

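### No adverse-event enquiry is scheduled during the three weeks on the diet, although Figure 1 marks diet-related events in that period and they are the primary safety outcome

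*Protocol*

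**What the plan says.** The protocol section *How will the outcome measures be measured at follow up?* names the sources: "Safety data will be ascertained via a combination of patient self-reporting and electronic medical record data". Questionnaires are used to "assess the presence of adverse events at baseline, the morning prior to surgery, and at 30-days postoperatively". For the chart, "Electronic medical records will be reviewed on the date of surgery and at 30-days postoperatively".

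The text of *What is the proposed frequency and duration of follow up?* places "symptom screening at the time of preoperative VLED initiation, the day of their surgery, and at 30-days following the date of their surgery". Figure 1 in the same section has a row "Intervention-associated adverse events", marked under -23 to -2, -2 to 0, 0 to discharge and +30. The first of these is the column in which the diet itself is marked.

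The section on allocating participants lists what the automated platform does. One task is to "send reminders to patients at the 1-week and 2-week points of the intervention period to remind patients to adhere to the study protocol". Another arranges an appointment with the research team after the intervention, with no content given. A third is to "send a follow-up email to patients two weeks after their scheduled surgery to ascertain whether any adverse events have occurred".

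The section on the steering and data monitoring committees commits to collecting and documenting all serious adverse events, and adds: "These data will be iteratively evaluated by the DMC". The outcomes section makes events attributed to the diet product the primary safety outcome, and safety of the diet is the fifth feasibility objective.

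**The concern.** The figure and the text do not match. Figure 1 shows diet-related events as an activity of the dosing period, but no section says how they would be picked up then. The first question after the diet starts comes when the course is finished or on its last day.

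The reactions that the protocol expects most often, from the large weight-loss trial it cites, are constipation, headache and dizziness. These come and go, and a single question three weeks later captures them poorly. The bias section already concedes that unblinded patients may bring recall bias to the symptom questionnaires. A pilot whose aims include showing that the diet is safe to give should also test a collection method fit for the definitive trial of 1,158 patients.

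**Working it through.** **1. Length of the course.** The compliance outcome prescribes 84 doses and the intervention section gives four packets a day: 84 / 4 = 21 days, which reproduces the stated three weeks. Counted by calendar, the treatment-period section runs from day -22 to day -1 and Figure 1 from day -23 to day -2. Each spans 22 days inclusive. The two windows differ by a day and should be reconciled, but the point does not depend on which applies.

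**2. Every scheduled contact set against that window.**

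| Contact | When | Adverse events asked about? |
|---|---|---|
| Questionnaire and symptom screen | Baseline / diet start | Yes, before exposure |
| Automated message | Week 1 | Not stated; adherence reminder |
| Automated message | Week 2 | Not stated; adherence reminder |
| Post-intervention appointment | After the intervention | Content not stated |
| Questionnaire, symptom screen, record review | Morning before, or day of, surgery | Yes |
| Automated email | Two weeks after the scheduled surgery date | Yes |
| Questionnaire, symptom screen, record review | Day 30 | Yes |

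Scheduled enquiries between diet start and the surgery-time questionnaire: 0. If that questionnaire is given on the morning of surgery, it follows the last dose. If it is given the day before, it falls on the last dosing day of the treatment-period section. The gap is about three weeks either way.

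**3. Recall.** If events fall evenly over a course of L days and are asked about once at its end, the mean delay is L / 2: 21 / 2 = 10.5 days, or 22 / 2 = 11 days. The maximum is the full three weeks.

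**4. Accrual while the first answers are awaited.** Assume even accrual at the planned 16 patients a month, a 30.4-day month and 1:1 allocation. Then 16 × 21 / 30.4 = 11.05 patients are randomised in one course length, and 8 × 21 / 30.4 = 5.5 of them to the diet (8 × 22 / 30.4 = 5.8 for 22 days). So about 11 more patients, five or six on the diet, enter before the first diet patient reaches a scheduled enquiry after starting.

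**5. What can reach the trial during dosing.** Three routes remain: unsolicited reports, the serious-event documentation, and the diabetes educator. The last covers diabetic patients in the diet arm only, and its stated purpose is medication management. The diet diary is filled in daily but handed over in a sealed envelope on the date of surgery, and control patients leave it blank.

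**6. Who is asked after the diet.**
- Completes the diet and has surgery: asked at surgery, by email and at day 30.
- Stops the diet and has surgery: asked at the same times, because follow-up does not depend on taking the product. The enquiry may come well after the event.
- Operation cancelled: unclear. The questionnaires are tied to surgery, the appointment has no stated content, and the email runs from the scheduled date, so it may or may not be sent.

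**The case against.** The best reply is that Figure 1's columns are periods. A mark under -23 to -2 may mean that events from that period count, with collection later. The adherence row is marked there too, although diaries are handed in on the day of surgery. That reading is possible and weakens the contradiction. It does not remove it: nothing in the text states it, and adherence at least has a daily record made in the period.

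Adverse events are recorded as present or absent, so a wrong date within the course does not change the outcome. That stands. An event forgotten altogether does change it. Weekly questions would also go to unblinded patients; they shorten recall but do not blind anyone. The diary, the diet instructions and the adverse-event document are not shown, so a prompt to report symptoms may exist in one of them. The protocol describes the adverse-event document as a list and definitions, not as a schedule.

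A reader might infer four stronger things that the documents do not support:
- *Patients who stop the diet are never asked.* They are, at surgery and at day 30.
- *Every enquiry after baseline hangs on the operation.* The appointment is defined by the intervention, and the email by a scheduled date.
- *The data monitoring committee cannot review iteratively.* Its commitment concerns serious events, all of which are to be documented, and it can review them across patients over about 5.5 months of enrolment.
- *Two or three serious events would be missed.* The cited rates applied to 44 diet patients give 44 × 0.045 = 2.0 and 44 × 0.078 = 3.4. They come from year-long and eight-week programmes, and the other 12 studies in the cited review reported no product-related serious events. Serious events are also the least likely to be forgotten, so this count does not measure under-reporting.

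**Conclusion.** The point holds as a gap in scheduled enquiry: none in about 21 days of dosing, for the outcome that the protocol names as its primary safety outcome. Its main effect is likely loss of minor, transient events through recall of up to three weeks. A second effect is that routine safety information on each patient arrives only at the end of that patient's exposure. The documents do not allow the under-reporting to be quantified. The 10.5 to 11 day mean delay assumes events spread evenly, and the count of about 11 further patients assumes even accrual at the planned rate. Coverage of patients whose operation is cancelled is unclear rather than absent. The change is worth making because it is cheap, not because the trial fails without it.

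**What to change.** 1. Add the same short adverse-event and symptom questions, for both arms, to the automated contacts already sent at weeks 1 and 2, through a link to the trial database form. Have replies handled by staff who are not blinded assessors.
2. State that the post-intervention appointment includes the adverse-event questionnaire and takes place at the end of the planned intervention period, even if surgery is cancelled.
3. Reconcile the four places: the platform tasks, Figure 1 with its text, the section on measurement at follow up, and the committee section. Say whether the mark in the dosing column means collection or attribution, and how the replies reach the data monitoring committee.

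The cost is protocol wording, two edited messages, a little staff time to review replies, and slightly more minor events recorded. Asking both arms the same questions keeps the comparison even.

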## What is the proposed sample size and what is the justification for the assumptions underlying the power calculations?

We propose a pilot RCT of 88 patients (i.e., 22 patients per site) to assess feasibility of a full RCT aimed at determining the efficacy of preoperative VLED at improving short-term postoperative outcomes in obese patients undergoing non-bariatric surgery. This sample size is sufficient to ascertain our feasibility objectives and is approximately 7.5% of the size of a definitive trial. A full RCT would require 1,158 patients (“Full Trial Power Calculation” document). We justified our proposed sample size of 88 patients based on 95% CIs for one of our feasibility outcomes. Specifically, to assess for 90% follow-up completion, 88 patients would provide 95% CIs of 82-95%, which we believe is adequate precision.

## What is the planned recruitment rate? How will recruitment be organized?

The anticipated recruitment rate will be 16 patients per month. Patient enrollment will continue until 88 patients are enrolled (i.e., approximately 5.5 months). There are over 200 elective non-bariatric abdominal surgeries performed monthly across the four included sites, and approximately 26.6% of Canadians are obese, which equates to approximately 53 patients per month that may be potentially eligible for enrollment.^50^ Moreover, there are over 400 elective orthopedic surgeries performed monthly across the four included sites, and given the same prevalence of obesity as above, this would equate to another approximate 106 obese patients per month that may be potentially eligible for enrollment.^50^ There are over 200 cardiac surgeries performed per month at our cardiac surgery center, equating to another 53 potentially obese patients eligible per month. Across Otolaryngology, Plastic Surgery, and Neurosurgery, there are at least another 200 elective cases performed per month, thus another 53 potentially eligible obese patients per month. Altogether, there will likely be over 250 potentially eligible patients per month.

All surgeons who perform elective non-bariatric surgery will be asked to consent to allow their patients to be approached. Patients will be identified from outpatient clinic schedules via the institution’s (i.e., Epic) or surgeon’s (e.g., Oscar) electronic medical record. Upon review of their chart, should the patient meet inclusion criteria and not meet any apparent exclusion criteria, they will be approached by research personnel who will provide further details with regards to the RCT. Recruitment will be organized and implemented by [name] and the research assistant(s) under the guidance of the coordinating center and steering committee.

## Are there likely to be any problems with compliance?

Adherence to a preoperative two-to-three-week regimen of preoperative VLED prior to bariatric surgery ranges from 80-90%.^51,52^ In our systematic review and meta-analysis evaluating the use of VLEDs in non-bariatric surgery, reported adherence ranged from 94-100% amongst the included studies, with much longer durations of intervention (0.46-24 weeks).^19^ As such, we feel as though compliance in the present study should be similar and is anticipated to range between 80% and 100%. In order to increase adherence with the study intervention, we will cover the cost of the Optifast® 900 or Medimeal® program and have patients complete a diet diary that they will submit following the three-week intervention period.

## What is the likely rate of loss to follow up?

We don’t anticipate a significant proportion of patients lost to follow-up in the present study given the small sample size, the short-term follow-up of one-month, and the lack of complicated and taxing study protocol for patients to adhere to. The aim of the present study to demonstrate feasibility is a study follow-up completion rate of greater than 90%. A follow-up completion rate of 80-90% will be considered feasible with modifications for the adequately powered RCT. A follow-up completion rate of less than 80% will suggest that a larger RCT is not feasible.

## How many centers will be involved?

This pilot trial will include four centers: 1) St. Joseph’s Healthcare Hamilton; 2) Juravinski Hospital; 3) Hamilton General Hospital; 4) Kingston Health Sciences.

## What are the proposed types of analyses?

Descriptive statistics (means, medians, standard deviations, interquartile ranges, proportions) will be used to characterize the study sample. The outcomes of the pilot study will be descriptive in nature and will focus on feasibility. Binary outcomes will be described using proportions with corresponding 95% CIs estimated using the Wilson Score method. Differences in continuous outcomes will be described using the difference in means with corresponding 95% CIs. Considering the feasibility nature of this pilot study, and following the 2010 CONSORT statement, we will not assess statistical significance for outcomes.^53^ We will calculate aggregated measures for 30-day postoperative morbidity to compare this to the tentative power calculation in the “Full Trial Power Calculation” associated document, to ensure an accurate power calculation is performed for the fully powered RCT. The proposed data analysis plan for the full RCT is reported in the “Full Trial Statistical Analysis Plan” associated document. Data will be analyzed using STATA statistical software (StataCorp version 15; College Station, TX). All data analysis will be completed by a blinded statistician.

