## What are the proposed practical arrangements for allocating participants to trial groups?

Patient recruitment will occur at Hamilton Health Sciences, St. Joseph’s Healthcare Hamilton, and Kingston Health Sciences. All surgeons who perform elective non-bariatric surgery at these sites will be made aware of the study via workshops and internal communications. Patients will be identified by the surgeons, their administrative assistants, and/or study investigators at the time of referral, at the time of their initial preoperative consultation, or some time following their initial preoperative consultation. Surgeons and/or other clinicians within a patient’s circle of care will introduce the study to participants at the time of their preoperative visits or sometime thereafter. Patients may also reach out directly to study investigators via the contact information provided on the study poster should they choose. Patients meeting inclusion criteria based on a review of their electronic medical record, which will only be accessed by persons within the circle of care or researchers that have obtained permission from the patient, will have their contact information (i.e., email and phone number) recorded and provided to designated research personnel at the time of their initial surgical consultation in clinic. This email contact information will then be passed into a novel automated clinical trials platform developed by Phelix AI©. This platform will automatically send an electronic version of the written informed consent document to the patient as well as a link to schedule an appointment in the following 1-2 days with the research team to discuss the informed consent document via telephone. If the Phelix AI© platform identifies that the patient does not have an accessible email address, this will trigger a notification to the research team and prompt them to call the patient by telephone. At the time of initial contact between the study personnel and patient, the study will be introduced, eligibility will be confirmed. Patients will be provided with the opportunity to ask questions about the previously circulated ICF, and if they have yet to review the document, they will review the document in its entirety with the research team at the time of the telephone contact. If, at the end of this process, patients are understanding of the material risks and benefits of participation, and wish to be enrolled in the study, they will sign the ICF and subsequently be randomized to one of the two arms in this parallel RCT. Following ascertainment of written informed consent, patients will be randomized via a web-based randomization system (randomization.net) in a 1:1 fashion to receive either standard of care plus preoperative VLED or standard of care alone. Randomization will be according to variable block sizes of four and six and will be stratified according to centre.

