4. Follow-up completion: Defined as completion of the pre-VLED, preoperative, and thirty-day postoperative visits, along with complete anthropometric measures and study questionnaires. A follow-up completion rate of greater than 90% will support the feasibility of a larger RCT. A follow-up completion rate of 80-90% will be considered feasible with modifications for the adequately powered RCT. A follow-up completion rate of less than 80% will suggest that a larger RCT is not feasible.

Safety Outcomes:

The primary safety outcome will be adverse events deemed secondary to the Optifast® 900 or Medimeal® programs. The adverse events will be recorded as dichotomous outcomes and described as either minor or serious, in a similar fashion to the OPTIWIN Study; the largest medical weight loss RCT evaluating Optifast®.^41^ Standardized definitions for minor and major adverse events are described in “Adverse Events” associated document. We will also measure patient frailty with grip strength at the time of anthropometric measurement.^43^

Clinical Outcomes:

The efficacy outcomes will include:

1. Overall 30-day postoperative morbidity. This will be defined as any deviation from the usual postoperative course within 30-days of the index operation and will be a composite of system-specific complications (see “Trial Outcome Definitions” document)
2. 30-day system-specific complications (see “Trial Outcome Definitions” document)
3. 30-day postoperative mortality
4. Preoperative weight loss. Preoperative weight loss will be assessed by measuring the post-VLED weight on the date of surgery and adjusting for the baseline weight in kilograms, as measured in a standardized fashion by a blinded research assistant.
5. Operative time. Operative time was chosen as an outcome as it is a commonly used objective surrogate for operative difficulty across various types of surgery.^44–46^ It has been used in previous bariatric RCTs as the primary outcome.^47^ Operative time will be measured as the time between first skin incision and closure of the last surgical wound in minutes and will be retrieved from the patient electronic medical record.
6. Intraoperative blood loss. This will be measured in milliliters and will be ascertained from the patient chart.

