7. Postoperative length of stay (LOS). This will be measured in days and will be ascertained from the patient chart. Postoperative LOS will be calculated as the number of days following the index surgery (i.e., postoperative day 0) that the patient remains in hospital. Every morning that the patient remains in hospital will count as an added day to postoperative LOS.
8. Quality of life. This will be assessed at baseline, following completion of the VLED, and 30-days postoperatively using the SF-36 (see associated “SF-36” document) administered by a blinded research assistant. The SF-36 has been validated in numerous previous cohorts of patients undergoing both non-bariatric surgery.^48,49^

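### The difference in means planned for continuous outcomes names neither the collected baseline values nor the centre stratum, and is not reconciled with the baseline-adjusted definition of weight loss (minor)

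*Protocol*

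**What the plan says.** The Protocol section *What are the proposed types of analyses?* gives one between-arm method for all continuous outcomes: "Differences in continuous outcomes will be described using the difference in means with corresponding 95% CIs". It names no covariate, change score or stratum, and it does not call the difference unadjusted. It also says that the pilot is descriptive and that significance will not be assessed.

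Three other statements bear on this:

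- In *What are the proposed primary and secondary outcome measures?*, preoperative weight loss is obtained by "measuring the post-VLED weight on the date of surgery and adjusting for the baseline weight in kilograms". Whether that means subtracting baseline or using it as a covariate is not stated.
- The same section says of quality of life: "This will be assessed at baseline, following completion of the VLED, and 30-days postoperatively using the SF-36". *How will the outcome measures be measured at follow up?* adds baseline values for waist circumference and grip strength.
- In the section on allocating participants, "Randomization will be according to variable block sizes of four and six and will be stratified according to centre". The centre section says "This pilot trial will include four centers".

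Operative time, blood loss and length of stay have no baseline value by their nature.

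**The concern.** Two analysts could follow this text and report different estimates. One, reading only the analysis section, could subtract mean day-of-surgery weights. The other, reading the outcome definition, could compare weight loss or fit a model with baseline weight. For SF-36 there is not even an outcome definition to settle the choice, because the Protocol does not say how its baseline enters the between-arm comparison. Centre was important enough to stratify on, yet the analysis section does not mention it.

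What is at stake is the width of the confidence intervals. With no significance assessment, these intervals are the pilot's only inferential output for the continuous outcomes. Information already paid for would go unused, and an unadjusted comparison of final values is also open to chance imbalance at baseline.

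**Working it through.** **The plan's own figure.** The only precision statement in the Protocol is for the follow-up criterion: "to assess for 90% follow-up completion, 88 patients would provide 95% CIs of 82-95" per cent. The Wilson score interval for p = 0.90 and n = 88 is 82.0 to 94.7%, so the figure is reproduced. It concerns a proportion, and nothing below changes it.

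**Inputs from the Protocol.** There are 88 patients, allocated "in a 1:1 fashion to receive either standard of care plus preoperative VLED or standard of care alone", hence 44 per arm, at four centres.

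**Inputs assumed.** The Protocol gives no standard deviation, no baseline-to-follow-up correlation r and no share of variance due to centre. I use r = 0.9 to 0.95 for weight, r = 0.3 to 0.7 for SF-36, and a centre share R² of 0 to 0.20. Equal standard deviations at both times and complete data are also assumed.

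**Formulas for the 95% half-width, in units of the outcome SD:**

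- Final value: t × √(2/44), with t on 86 degrees of freedom = 0.424
- Change from baseline: 0.424 × √(2(1 − r))
- Linear model with baseline (ANCOVA): t on 85 degrees of freedom × √(2/44) × √(1 − r²)

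| r (assumed) | Final value | Change | ANCOVA | Final ÷ ANCOVA | Change ÷ ANCOVA |
|---|---|---|---|---|---|
| 0.3 | 0.424 | 0.501 | 0.404 | 1.05 | 1.24 |
| 0.5 | 0.424 | 0.424 | 0.367 | 1.15 | 1.15 |
| 0.7 | 0.424 | 0.328 | 0.303 | 1.40 | 1.08 |
| 0.9 | 0.424 | 0.190 | 0.185 | 2.3 | 1.03 |
| 0.95 | 0.424 | 0.134 | 0.132 | 3.2 | 1.01 |

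Adding three centre terms (82 degrees of freedom) changes these ANCOVA widths by at most 0.001 SD if centre explains nothing.

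**Weight (r = 0.9 to 0.95).** Raw final weights give intervals 2.3 to 3.2 times as wide as ANCOVA. Change from baseline gives intervals only 1 to 3% wider. In kilograms, with an assumed SD of 20 kg, the half-widths are:

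- raw final weight: 20 × 0.424 = 8.5 kg
- change: 3.79 kg (r = 0.9) and 2.68 kg (r = 0.95)
- ANCOVA: 3.70 kg and 2.65 kg

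With an SD of 15 or 25 kg the raw figure is 6.4 or 10.6 kg.

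**SF-36.** Against final scores, ANCOVA narrows the interval by 1 − √(1 − 0.5²) = 13% at r = 0.5 and by 1 − √(1 − 0.7²) = 29% at r = 0.7. At r = 0.3 the gain is about 5%. A change score is no substitute here: it equals the final score at r = 0.5 and is wider at r = 0.3 (0.501 against 0.424). Because (1 − r²) = (1 − r)(1 + r) and 1 + r ≤ 2, ANCOVA is never less precise than the change score, apart from the small cost of estimating the extra coefficients.

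**Centre.** The ratio of adjusted to unadjusted width is about √(1 − R²), with t on 83 degrees of freedom: 1.00 at R² = 0, 0.975 at 0.05, 0.95 at 0.10 and 0.89 at 0.20. Intervals are therefore 0 to about 11% narrower.

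**The case against.** A reader might infer that the Protocol contradicts itself, and that the weight result would be nearly useless: a half-width of 8.5 kg under the assumed SD of 20 kg, when the section *Why is a trial needed now?* cites losses from 3.2 kg upward. The documents do not support this. The listed outcome is preoperative weight loss, not final body weight. A difference in mean change, or a baseline-adjusted mean difference, satisfies both sections, and the word unadjusted appears in neither. On the change reading the precision lost for weight is about 1 to 3%, and each patient's starting weight is already removed.

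A reader might also take weight loss as the pilot's main check on the intervention. The Protocol does not say so. Feasibility is primary, and the criterion tied to the intervention is diary compliance. The sample size rests on follow-up completion. The clinical quantity carried into the full-trial power calculation is 30-day morbidity, not a continuous outcome. Waist circumference and grip strength are not among the eight efficacy outcomes. All of this stands, and it keeps the point minor.

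The remaining objection is that covariates are commonly left to a statistical analysis plan, which is not shown here. That stands only in part. The analysis section does fix a method for continuous outcomes, in the same paragraph that names the Wilson method for proportions. The point is that this stated method can be improved and should be aligned with the weight definition, not that detail is missing.

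On centre, no variance share is given and the effect may be nil. The recruitment section places cardiac surgery at one centre, which makes a difference in case mix plausible but gives no size for it.

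**Conclusion.** The point holds as an unreconciled specification and a free gain in precision, of minor severity. For weight, the loss is large only if raw day-of-surgery weights are compared; on the more natural change-from-baseline reading it is negligible. The firmer gain is for SF-36, where neither final scores nor change scores match ANCOVA over the assumed correlations. The gain from centre is unknown and may be zero. All sizes rest on assumed correlations, standard deviations and centre shares, on equal variances at both times, and on complete data at 44 per arm. The stated 82 to 95% interval, the sample size and every feasibility threshold are unaffected.

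**What to change.** Replace the sentence on continuous outcomes in *What are the proposed types of analyses?* with:

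> *Between-arm differences in day-of-surgery weight and in SF-36 scores (and in waist circumference and grip strength, if compared) will be estimated with 95% CIs from a linear model with treatment arm, the baseline value and centre as terms. Operative time, blood loss and length of stay will be compared in a linear model with treatment arm and centre. No p-values will be reported.*

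In the definition of preoperative weight loss, add that the baseline adjustment is the one in this model. The change costs one sentence and a cross-reference. It needs no new data, visits or patients, keeps the descriptive intent, and should be made before anyone sees outcomes by arm.
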